## Economic evaluation

A full economic evaluation will be conducted as part of this study:At 3 years of follow up, alongside the primary RCT outcome measure, andBased on an extrapolation of trial outcomes over a patient’s life-time, using an appropriate Markov decision analysis model to explore longer term cost-effectiveness.

The primary economic evaluation will be in the form of a cost-benefit analysis, reporting net benefit (Willingness To Pay (WTP) - cost), with WTP elicited using a Discrete Choice Experiment (DCE). We have chosen a cost-benefit analysis (CBA), as opposed to a traditional analysis of cost per generic EQ-5D QALY as the primary economic outcome measure because of concerns that generic QALYs are not sufficiently sensitive to capture the processes and outcomes of dental treatments. The CBA is therefore the outcome of most interest in terms of investigating value for money (efficiency) of prescription of high concentration fluoride toothpaste. In addition to the primary health economic analysis, two further analyses will be undertaken as secondary economic outcomes to inform various stakeholders:NHS decision makers, such as NICE may be interested in the cost of achieving gains in quality adjusted life years (QALYs) and therefore recommend the conduct of a cost per QALY analysis for technology appraisal. In order to comply with these recommendations, we will include the generic EQ-5D-5L health profile measure at baseline and each follow up time point in the trial. This will enable the calculation and presentation of the mean cost per additional QALY as a secondary health economic outcome.Dental practitioners may be interested in the cost of achieving various specific clinical outcomes. We will therefore complete a cost-effectiveness analysis, based on the primary clinical outcome measure for the trial, reporting cost per episode of dental treatment avoided (i.e. the cost per filling or extraction avoided). A further secondary analysis will present cost per DMFS avoided.

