## Outcome measures

### Primary outcome

The proportion of participants receiving any dental treatment due to caries; including restorations, endodontics or extraction. Any dental treatment provided and the reasons for providing treatment (caries, tooth wear or other e.g. trauma) will be recorded. The primary outcome (treatment directly due to caries) will be extracted from the Clinical Report Form (CRF).

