### Economic outcomes

Provision of NHS and privately-funded dental treatments will be collected from the CRF. In addition we will also collect information on NHS treatment completed using routinely collected NHS data held by the ISD, BSA and BSO. Treatment cost data will be collected for participants from 1 year prior to randomisation until the end of the trial.All remaining resource use data will be collected using questionnaires provided to participants on attendance for dental care or mailed to participants who fail to attend. These will include the use of other NHS healthcare services (e.g. GP visits, dental hospital attendances and other healthcare resource use) directly related to dental problems as well as data on non-NHS costs (e.g. time and travel costs, time off work, privately purchased care, self-purchased dental care products).Collection of EQ-5D-5 L will enable the calculation of the mean cost per additional QALY as a secondary health economic outcome.A discrete choice experiment (DCE) with an online representative sample of the UK general population (aged 50 and over) will be undertaken to elicit willingness to pay (WTP) for high fluoride toothpaste and associated patient relevant outcomesLong term economic evaluation with trial results extrapolated over a life-time horizon using Markov modelling methods

The methods used to collect the various outcome measures are summarised in Table 1.

**Table 1 Tab1:** Summary of methods used to collect outcome measures

	Baseline	Elective and non-elective visits to the dentist over 3 year follow up^a^	36 months	Annual Questionnaire	National Database
Clinical Status (full dental chart)	○	○	○		
Treatment details Check ups, restorations, endodontics, extractions (reason for treatment in CRF and all NHS treatments in national datasets) Prescription of toothpaste (date and amount prescribed) Relevant medical history and medication	○	○			X
Healthcare costs GDP completed CRF: payment mechanism (NHS/private) and charges levied Dental treatment received in other settings (patient element of CRF) NHS costs from national data sets Non NHS treatment costs in patient element of CRF)	○	○	○		X
Detailed independent clinical assessment ICDAS, BoP (Scotland only)	○		○		
EQ-5D-5 L	○			●	
OHIP-14	○			●	
Pain - seeking professional care because of pain	○	○			
Oral health behaviour	○			●	
Redemption of toothpaste prescriptions	○	○	○		X
Adverse reactions		○			

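### The secondary cost-effectiveness ratio is tied to a yes/no outcome per participant but reported per filling or extraction avoided, which needs a count of treatments

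*Protocol article*

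**What the plan says.** The protocol article, under *Primary outcome*, defines the outcome as "The proportion of participants receiving any dental treatment due to caries; including restorations, endodontics or extraction". *Sample size considerations* treats it as a proportion, 75% v 65% at 36 months.

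*Economic evaluation* makes cost-benefit the primary economic analysis. It adds two secondary ones, a cost per QALY and a cost-effectiveness analysis aimed at dental practitioners. The latter is described as "based on the primary clinical outcome measure for the trial, reporting cost per episode of dental treatment avoided", with the unit then explained as "the cost per filling or extraction avoided". A further ratio, per DMFS avoided, is mentioned separately.

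On data, *Primary outcome* also states: "Any dental treatment provided and the reasons for providing treatment (caries, tooth wear or other e.g. trauma) will be recorded". *Economic outcomes* states: "Provision of NHS and privately-funded dental treatments will be collected from the CRF". Table 1 in that section lists the treatment types, with the reason for treatment taken from the CRF.

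**The concern.** The description joins two different units. The primary outcome counts people: a participant with one filling and a participant with five each contribute one event. A cost per filling or extraction avoided counts treatments. Dividing incremental cost by the difference in the primary outcome gives the cost of keeping one participant entirely free of caries treatment, which is a different quantity.

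The event set differs too. The primary outcome includes endodontic treatment; the explanation of the ratio names only fillings and extractions.

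The ratio is offered to practitioners, who would naturally read it as a price for avoiding one filling. If the participant-level difference were used under the treatment-level label, that price would look too high wherever the intervention avoids more treatments than it spares participants.

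**Working it through.** **Step 1: confirm that the primary outcome is binary.** Inputs from *Sample size considerations*: 75% v 65%, two-sided 5%, 90% power, 25% attrition. With pooled variance under the null and no continuity correction:

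n = [1.960 × √(2 × 0.70 × 0.30) + 1.282 × √(0.75 × 0.25 + 0.65 × 0.35)]² / 0.10² = (1.270 + 0.826)² / 0.01 ≈ 439.2, rounded up to 440 per group. Then 440 / 0.75 = 586.7, rounded up to 587.

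Both figures match the article, so the outcome is planned as one yes/no result per participant.

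**Step 2: write down the two ratios.** Let ΔC be the incremental cost per participant, and m_C and m_I the mean number of caries treatments per participant in the control and intervention groups.

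- From the primary outcome: ΔC / (0.75 − 0.65) = ΔC / 0.10, the cost per participant kept free of caries treatment.
- From a count: ΔC / (m_C − m_I), the cost per treatment avoided.

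If the first were labelled as the second, the overstatement factor would be (m_C − m_I) / 0.10.

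**Step 3: size under stated assumptions.** The article gives neither m_C nor m_I. The planned proportions fix only the share with no treatment: P₀ = 0.25 (control) and 0.35 (intervention). The means then depend on an assumed distribution:

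- Constant t treatments per treated participant, the same in both groups: m = t(1 − P₀)
- Poisson: m = −ln P₀
- Negative binomial, same k in both groups: m = k(P₀^(−1/k) − 1)

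| Assumption | m_C | m_I | Avoided | Factor |
|---|---|---|---|---|
| Constant, t = 1 | 0.75 | 0.65 | 0.10 | 1 |
| Constant, t = 2 | 1.50 | 1.30 | 0.20 | 2 |
| Constant, t = 4 | 3.00 | 2.60 | 0.40 | 4 |
| Poisson | 1.386 | 1.050 | 0.336 | 3.4 |
| Negative binomial, k = 5 | 1.598 | 1.168 | 0.429 | 4.3 |
| Negative binomial, k = 2 | 2.000 | 1.381 | 0.619 | 6.2 |
| Negative binomial, k = 1 | 3.000 | 1.857 | 1.143 | 11.4 |

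The factor is also 1 if the intervention's only effect is to spare 10% of participants a single treatment each (0.10 × 1 = 0.10), whatever happens to the others.

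**Step 4: illustration.** For an assumed ΔC of £100, the first ratio is 100 / 0.10 = £1,000 per participant kept treatment-free. Under Poisson counts the second is 100 / 0.3365 ≈ £297 per treatment avoided.

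**The case against.** The strongest reply is that the section never says incremental cost will be divided by the risk difference. It gives the unit twice, per episode and per filling or extraction, and an analyst following those words would have to count treatments. On that reading, the reference to the primary outcome only names the type of event, to set this ratio apart from the QALY and DMFS ratios. The data for a count exist, since treatments and their reasons are recorded. The article is also a condensed account, and a fuller economic plan may define the denominator.

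Much of this stands. A reader might infer that the published ratio will be several-fold wrong. The documents do not support that: an error arises only if the risk difference is actually the divisor, and its size depends on treatment counts that the article does not give. How a count would be modelled can properly be left to a fuller plan.

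The mismatch in the text remains. It is not missing detail, because the article states both the basis and the unit, and they conflict. A plan that counts treatments departs from the stated basis; a plan that uses the primary outcome makes the label wrong. Elsewhere the article keeps the two units apart: for dental pain, *Secondary outcomes (patient reported)* asks both for any episode and for the total number per participant.

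**Conclusion.** The concern holds as an inconsistency between the stated basis and the stated unit of a secondary economic ratio, with endodontics dropped from the explanation as well. If the participant-level difference were used under the existing label, the cost of avoiding one treatment would be overstated by a factor that the documents cannot fix. The assumptions shown give 1 to 4 for a constant number of treatments per treated participant, 3.4 for Poisson counts, and about 6 and 11 for negative binomial counts with k = 2 and k = 1. All of them use the planned 75% v 65%. A several-fold error is therefore possible but not established.

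The consequence is limited to this ratio. The sample size, the primary clinical analysis and the primary cost-benefit analysis do not depend on it. The wording should still be settled before the analysis, so that the denominator is not chosen after the results are known.

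**What to change.** Amend the cost-effectiveness item in *Economic evaluation* in one of two ways.

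(a) Use as denominator the difference in the mean number of caries-related restorations, endodontic treatments and extractions per participant over 36 months, derived from the CRF, and stop describing it as the primary outcome measure.

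(b) Keep the primary outcome as the basis and label the ratio 'cost per participant kept free of caries treatment'.

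Both ratios may be reported if each carries its own label. Option (a) costs one derived variable from data already collected, plus a sentence; option (b) costs a change of label. Listing the count as a formal secondary outcome of the trial is optional.

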### Estimation of costs

Costs will be estimated from both an NHS and patient perspective. NHS costs of providing the high fluoride toothpaste intervention will be based on the costs of dispensed prescriptions verified by BSA, BSO & ISD in England, Northern Ireland and Scotland respectively. Methods for the collection of resource use data for cost estimation over the trial follow up are summarised in Table 1. All resource use data will be costed at the patient level, using region specific tariffs, and aggregate costs applied across these three settings, with sensitivity analyses presenting data for each setting separately.

Data on costs for each area of service use will be summed to provide a mean cost per patient participant (from both an NHS and patient perspective). Incremental costs per patient for high dose fluoride toothpaste vs usual care will be estimated using generalised linear models with appropriate distributions for cost data and adjustment for baseline covariates, such as gender and age. The costing analysis will include a statement on budget impact of alternative policy approaches.

### Cost-Benefit Analysis – willingness to pay (WTP)

Whilst health based outcomes are of importance for funders of dental care, there is a growing interest in wider measures of value, which go beyond traditional QALY approaches and offer a more holistic and sensitive measure of value. It is crucially important for adherence, and hence real-world cost-effectiveness, that any public health intervention is not only valued in terms of health outcomes within a clinical trial, but also has wider generalisability to the consumers of the intervention. We will therefore conduct a cost-benefit analysis (CBA) reporting benefits in terms of WTP to obtain a more holistic measure of value. WTP will be obtained from a discrete choice experiment (DCE) [27], conducted with a nationally representative sample of the general population (aged 50 and over), to explicitly value the provision of high fluoride toothpaste, together with a range of plausible outcomes from the trial (e.g. avoidance of caries progression). The DCE will explicitly value the high fluoride toothpaste intervention, together with associated health outcomes and other important attributes.

The DCE will include a cost attribute. By including this attribute, the willingness to pay (WTP) for a change in the level of any other attribute will be estimated. Estimates of WTP derived from the DCE will be combined with the intervention (provided or not) and clinical outcome data from the trial to report net benefit [mean WTP – mean cost [28]] for high fluoride toothpaste compared to standard care. If benefits are greater than the costs, then high fluoride toothpaste would be deemed an efficient use of resources.

Results will be presented on a cost-benefit plane, illustrating the probability that the intervention is associated with positive or negative net benefit. A comprehensive set of sensitivity analyses will be undertaken to explore uncertainty in our conclusions. These will include assumptions surrounding missing data, the estimation of costs and the effect of different payment / co-payment structures on the cost-benefit results.

### Decision modelling

The “within trial” economic analyses will assess and report on the costs and outcomes of high fluoride vs. standard treatment up to 3 years post-randomisation. However, the true economic value of an intervention depends on the long-term implications of that intervention. We will develop a de novo Markov decision analysis model, to extrapolate the trial outcomes over a longer, life-time horizon [29]. Results will be reported using a cost-effectiveness framework and estimates of WTP from the DCE will be used to explore results using a similar cost-benefit framework to that used for the primary trial based economic analysis. The final model structure and health state definition (e.g. caries progression, new caries, and tooth loss) will be developed in conjunction with dental experts. National cohort datasets, such as the adult dental health survey, and other longitudinal studies will be used as a source of baseline transition probabilities. Sensitivity analysis will use the data from the control (standard care) arm of the trial. Where possible, survival analysis methods will be used to assess the time to transition between health states in each of the study arms, with survival curves fitted over an extended time frame (patient’s life time). Data from cohort studies and literature reviews will be used where necessary to supplement extrapolation models to determine long run caries progression.

Cost data for health states beyond trial follow up will be sourced from the trial data and routine data sources (ISD/BSA/BSO) for appropriate treatment in the respective model health states. To inform a life-time cost-benefit analysis, estimates of WTP will be sourced directly from the DCE conducted alongside the trial for specific health states (e.g. WTP to avoid caries progression, new caries or tooth loss). The model will be developed at an early stage in the study to ensure all relevant data to populate the model are collected within the trial. All modelling assumptions will be extensively tested using sensitivity analyses and the model will be fully probabilistic. Key gaps in the evidence base will be identified and their potential impact on cost-effectiveness explored. Results will be presented using standard economic evaluation approaches to illustrate uncertainty. Threshold analyses will be conducted to indicate the values required for key model parameters to change economic evaluation results. Patients will be consented to obtain longer-term data linkage to routine records, which can then be used for future validation of the extrapolation assumptions.

## Research governance, data protection and sponsorship

The trial will be run under the auspices of CHaRT based at HSRU, University of Aberdeen. This will aid compliance with Research Governance, and provide centralised trial administration, database support and economic and statistical analyses. CHaRT is a registered Clinical Trials Unit with particular expertise in running multicentre RCTs of complex and surgical interventions. The Sponsor and CI will ensure, through the TSC, that adequate systems are in place for monitoring the quality of the trial (compliance with appropriate governance) and appropriate expedited and routine reports, to a level appropriate to the risk assessment of the trial.

The Trial Co-ordinating Office (TCOD) based in the Dundee Dental School and Hospital, University of Dundee will provide day-to-day support to the GDPs and outcome assessors/research nurses. The Trial Office Teams at TCOD and CHaRT will meet formally approximately monthly during the course of the trial to ensure smooth running and trouble-shooting.

Data collected during the course of the research will be kept strictly confidential and accessed only by members of the trial team. Participants’ details will be stored on a secure database under the data protection guidelines and regular checks and monitoring are in place to ensure compliance. Data will be archived to a secure data storage facility. The CTU senior IT manager (in collaboration with the Chief Investigator) will manage access rights to the data set. Participants will be allocated an individual specific trial number and their details will be anonymised on the secure database. We anticipate that anonymised trial data may be shared with other researchers to enable international prospective meta-analyses.

Manchester University NHS Foundation Trust is the sponsor for the trial. An independent risk assessment was carried out by the Sponsor prior to commencement of the trial and will be reviewed and, if necessary, updated annually for the duration of follow up. The trial will be monitored to ensure that the study is being conducted as per protocol, adhering to Research Governance, and the appropriate regulations. The approach to, and extent of, monitoring will be specified in a trial monitoring plan which will be determined by the risk assessment of the study and updated if necessary following the outcomes of the annual risk assessment review.

The Sponsor will provide indemnity for non-negligent harm. All dentists and dental care professionals working on the trial will be registered with the General Dental Council and have appropriate indemnity arrangements in place.

### Data-handling, record keeping and archiving

Clinical data will be entered into the trial database by the TCOD together with data from questionnaires completed at clinic. Questionnaires returned by post to the trial office will be entered there. Staff in the trial office will work closely with practices to ensure that the data are as complete and accurate as possible. Extensive range and consistency checks will further enhance the quality of the data. The Sponsor is responsible for ensuring that trial data is archived appropriately. Essential data shall be retained for a period of at least 15 years following close of trial.

### Satellite studies

It is recognised, that the value of the trial may be enhanced by smaller ancillary studies of specific aspects. Plans for these will be discussed in advanced with the Project Management Group. REC approval will be sought for any new proposal, if appropriate.

## Dissemination

This trial will produce new knowledge which will be valuable to key stakeholder groups: patients, policy makers, dental healthcare providers and commercial organisations both in the UK and internationally. We intend to maintain interest in the trial by publication of newsletters at intervals for staff and collaborators. Once the main report has been published, a lay summary of the findings will be sent in a final Newsletter to all involved in the trial.

We will develop our dissemination strategy as the trial progresses with our PPI group and engagement with stakeholder groups. The key stakeholders will be:Policy makers, guideline producers and commissioners: the four Chief Dental Officers (CDOs), NICE, SIGN, SDCEP and Public Health England. At the end of the trial we intend to hold a workshop for policy makers and produce summary briefing documents of our findings. The trial team will liaise with the editorial team from the Cochrane Oral Health Group to ensure the timely update of the relevant Cochrane reviews. We will engage with international bodies and organisations such as, WHO, US Centre for Disease Control, FDI.Clinicians: we will speak at national clinical conferences, relevant dental specialist society meetings and produce clinical summary papers in popular journals read by clinicians.Patients and the public: we will issue press releases to the popular media and post lay summaries of the outcomes on our web sites and engage with the public through social media.Academic community: the principal output will be a monograph published in accordance with NIHR guidelines on project outputs [30] in the funder’ journal. In addition, we will aim to publish our findings in peer-reviewed, high impact, internationally-leading journals. We will present our findings at relevant national and international oral health conferences such as IADR.Industry and commerce: We will provide reports for major toothpaste manufacturers.

## Discussion

The Reflect Trial is an NIHR HTA funded trial that is being undertaken across England, Northern Ireland and Scotland. It is a pragmatic, multi-centre, open-label randomised trial designed to determine whether or not the substantial and rapidly increasing costs of prescribing high fluoride concentration toothpaste benefits patients and represents a wise investment for the UK National Health Service. The trial is pragmatic in nature, designed as far as possible to mirror ‘real life’. This pragmatic approach is reflected in:the population: involved in the trial, high caries risk older adults, have been identified by national guidance in England as a key target group for prescribing high concentration fluoride toothpaste [12]the intervention: prescription of high concentration fluoride toothpaste. 5000 ppm fluoride toothpaste was chosen, as this higher concentration is likely to produce the largest effect size (compared to 2800 ppm fluoride toothpaste). The intervention tests the prescription of the drug by GDPs rather than the drug being directly provided to participants. Therefore decisions taken by dentists on the amount and frequency of prescribing the drug and the compliance of participants in using the toothpaste need to be measured and considered in the analysis and interpretation of results.the primary outcome measure: receipt of treatment as a result of caries was determined by patient and public involvement as a key concern of patients. More traditional measures of caries are included as secondary outcome measuresthe comparator: the intervention will be compared to ‘usual practice’ as determined by each participant’s dentist.

Importantly the setting for the trial is primary care dental practices, where the overwhelming majority of patients receive their dental care. Participants will be recruited in approximately 60 practices across the three countries, providing a varied range of practices operating in different geographical environments and socio-economics circumstances and different remuneration systems. This broad range of practices should ensure the results of this trial are widely applicable. The evidence base for high concentration fluoride toothpaste is not strong both in terms of both efficacy and for how well this health technology works in day-to-day general dental practice. The results of this pragmatic trial should complement the findings of efficacy trials to provide high quality evidence on the costs and benefits of high concentration fluoride toothpaste to support the decisions of dental practitioners, patients and policy makers on its use.

The team responsible for the design and delivery of the trial is multidisciplinary drawn from a strong collaboration between the Universities of Aberdeen, Dundee and Manchester plus colleagues working in the NHS and local research networks. The trial is a Clinical Trial of a Investigative Medicinal Product and is overseen by the trial sponsor Manchester University Foundation Trust, supported by an independent Trial Steering Group and Data Management Committee and Patient and Public Involvement Group. This will ensure that the trial is conducted to the highest standards. We expect the Reflect Trial to make an important national and international contribution to understanding the role that high concentration fluoride toothpaste can play in the management of high caries risk in older adults attending primary dental care.

